#### Participants and Recruitment

Participants for stage 3 are recruited via the same 2 pathways as described in stage 2 (ie, CDCN and clinician flyer with survey link), using convenience sampling to recruit as many eligible participants living with iMCD as possible. An ideal target sample size is ≥100, as simulations have suggested that samples of 100 and above produce more stable estimates in advanced psychometric analyses used in PROM development, such as Rasch model analysis [49]. To maximize the pool of potential recruits, patients who participated in stage 2 will be invited to participate in stage 3. Nevertheless, a sample of 100 may not be achievable given the rarity of the condition. Instead, an absolute minimum target sample size of 50 is adopted, as there is some evidence that this is a reasonable absolute minimum for conducting exploratory factor analysis [50]. Psychometric analyses will be adapted, as appropriate, to the final sample size (details provided in the Analysis subsection). Recruitment will continue until the minimum target sample is achieved.

As part of additional exploratory work for one of the project collaborators, English-speaking patients will be recruited from a health care site in Brazil. They are required to self-declare at least a B2 English language level [51]. These participants will be included in exploratory analyses only and not as part of the PROM development described in this protocol.

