#### Data Collection

Survey content (Multimedia Appendix 1) will be agreed on alongside the PAG and clinical advisors prior to launch. The setting for the survey will be online to maximize recruitment numbers in a rare disease. Research suggests that electronic and paper-based PROM administration is broadly equivalent [43], and changing the mode of administration represents a minor to moderate modification that is unlikely to have a significant impact on scores [52]. However, it should be transparently acknowledged that mode of administration can affect who completes the survey (ie, the sample characteristics) [53,54].

After following a link to the online survey, participants provide informed consent and complete the iMCD screener described in stage 2. Those who pass the screener are considered eligible and proceed to answer sociodemographic and clinical background questions (ie, age, gender, country of residence, employment status, educational level, ethnicity, relationship status, age at the time of iMCD diagnosis, and iMCD treatment). Participants are then asked a single question on the impact of their iMCD symptoms on their daily activities (split into 3 options: no symptoms, symptoms but no impact on daily activities, and symptoms that are impacting daily activities).

Following these background questions, participants complete a draft version of the ISBUS PROM. Participants are then asked to rate the perceived importance of including each draft PROM symptom item in the final questionnaire on a 4-point Likert scale (0=not at all important; 3=very important). Participants then complete a 100-point visual analog scale with the stem, “Thinking about iMCD, how would you rate your quality of life during the past seven days?” (0=worst imaginable quality of life; 100=best imaginable quality of life). Next, participants are asked to complete the Patient Health Questionnaire-15 (PHQ-15), which measures physical symptoms [55], and the EQ-5D-5L (which measures health status [56]) for their country (US English was used for Brazil). Finally, participants are asked to leave their email address for reimbursement and to be contacted about participation in stage 4. Participants receive an Amazon e-voucher for taking part in the study (in their respective currency).

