#### Analysis

Table 2 outlines the planned psychometric analyses to be conducted as part of the ISBUS project. Analyses will be adapted to the actual sample size achieved (ie, ≥50 or ≥100) and will include, at the very least, exploratory factor analysis to assess structural validity; correlations and group comparisons for construct validity; and Cronbach α for internal consistency. Given the small sample size expected and the likely skewed distribution, it is anticipated that nonparametric statistics will be used (eg, Spearman ρ correlations and unweighted least squares estimation) [20,57].

**Table 2 table2:** Planned psychometric analyses for the ISBUS^a^.

Stage and measurement property		Analysis	Evaluative criteria
Stage 3: final item selection			
	Structural validity		
		If n≥50 but <100: exploratory factor analysis using unweighted least squares for small samples	Loadings ≥0.40 Communalities ≥0.30 Chi-square test *P*>.5 RMSEA^b^<0.08 TLI^c^≥0.90 RMSR^d^≤0.08
		If n≥100: CFA^e^ or EFA^f^; Rasch modelling	CFA: same criteria as EFA Rasch: fit residuals between −2.5 and 2.5 Ordered thresholds
	Hypothesis testing for construct validity		
		Correlate ISBUS burden score with iMCD^g^ quality of life VAS^h^, PHQ-15^i^ score, and EQ-5D-5L utility	At least moderate correlations (rs≥0.30)
		Compare participants with symptoms impacting daily activities vs those without such impact	At least a moderate difference (d≥.05)
	Internal consistency		
		Cronbach α	Cronbach α≥0.70
Stage 4: preliminary measures of change			
	Test-retest reliability		
		ICC^j^ in participants reporting no change in health status	ICC≥0.70
	Measurement error		
		Standard error of measurement and MDC95^k^ in participants reporting no change in health status	MDC95<MIC^l^
	Responsiveness		
		SRM^m^ for improved, stable, and worsened group	SRM≥0.2 (improved and worsened group) and <0.2 (stable group)
		ROC AUC^n^ for improved subgroup	ROC AUC≥0.70 (improved group)
	Meaningful change (MIC)		
		Anchor-based MIC (mean and median improvement) for the minimally improved group	Correlation between anchor and change ≥0.30
		Distributional analyses (0.5 × SD, standard error of measurement) in the improved health group	MIC>MDC95
		Responder difference (mean and/or binary method)	More responders in the improved group than in the nonimproved group

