## Results

The ISBUS project was funded in June 2023 and is ongoing at the time of submission. Stage 1 (item generation) began at the start of the project and concluded in December 2023. Stage 2 (item testing and refinement) started in January 2024; interviews with people living with iMCD (n=10) were conducted between May 2024 and September 2024, and this stage concluded in November 2024. Stage 3 began in December 2024. The first survey participant was enrolled in February 2025, and recruitment continued until November 2025, with 51 people living with iMCD completing the survey. Stage 3 concluded in January 2026, when the symptom burden scale was finalized. However, recruitment in Brazil (which is being used for comparative purposes only) is ongoing. Stage 4 is ongoing. As of March 2026, when the paper was submitted, 32 people had completed a follow-up survey, and the qualitative interviews on meaningful change were ongoing. A scale development paper (featuring the results from stages 1-3) is expected to be published in 2026, with a further paper on understanding change (stage 4) published in 2027. In accordance with established best practice [17], a user manual will be produced for the new PROM describing, among other aspects, how to score and administer the measure.

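### The known-groups criterion in Table 2 is labelled a moderate difference but printed as d≥.05, a tenth of the conventional moderate value, so that row says almost nothing by itself

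*Protocol article*

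**What the plan says.** In the protocol article, the stage 3 part of Table 2 (Planned psychometric analyses) has two rows under hypothesis testing for construct validity.

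- **Correlations.** The ISBUS burden score is correlated with the iMCD quality-of-life visual analogue scale, the PHQ-15 and the EQ-5D-5L utility. The criterion is "At least moderate correlations (rs≥0.30".
- **Known groups.** The instruction is "Compare participants with symptoms impacting daily activities vs those without such impact", and the criterion is "At least a moderate difference (d≥.05".

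The grouping comes from a single survey question, described under stage 3, Data Collection, as "split into 3 options: no symptoms, symptoms but no impact on daily activities, and symptoms that are impacting daily activities". The article does not say how many participants fall in each group.

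On sample size, stage 3, Participants and Recruitment, states "An ideal target sample size is ≥100" and then "an absolute minimum target sample size of 50 is adopted". The Results section reports that "recruitment continued until November 2025, with 51 people living with iMCD completing the survey".

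For standardised change in stage 4, the same table uses "SRM≥0.2 (improved and worsened group) and <0.2 (stable group". No other section gives a different d threshold or defines a moderate d.

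**The concern.** The words and the number in one criterion disagree by an order of magnitude. A d of .05 is a twentieth of a standard deviation, which nobody would call moderate.

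The number is what a reader or analyst would compare the estimate with, so the mismatch sits in the decision threshold itself. Taken literally, the row would often credit the scale with separating people whose symptoms affect daily activities from those whose symptoms do not, even when it does not separate them.

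This matters because the abstract names known-group validity as one of the two construct-validity methods, and because the scale is meant to serve as a secondary end point in trials. The paper reporting stages 1-3 is still to appear and will be read against this published criterion.

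**Working it through.** The threshold is stated, not derived, and the article gives no power calculation for this comparison, so there is no figure to reproduce. The check asks what the printed threshold lets through.

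**Inputs**
- Threshold as printed: c = .05 (Table 2).
- Comparison threshold: c = 0.50. This is the usual convention for a moderate d and is not stated in the article.
- N = 51 achieved (Results). The minimum of 50 and ideal of 100 serve as sensitivity values.
- Group split: an assumption, since none is given. Main range 26/25 to 41/10, with 46/5 as an extreme.
- Direction: Table 2 prints none. The main reading is that the group with impact on daily activities scores higher.

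**Step 1: label against number**
- 0.50 / .05 = 10.
- Table 2's moderate correlation converted to d for equal groups: d = 2r/√(1−r²) = 0.60/√0.91 = 0.63. In reverse, d = .05 corresponds to r = .05/√(.05²+4) = 0.025.
- Table 2 treats a standardised response mean below 0.2 as stable. Its denominator differs from that of d, so this is a rough yardstick only, but .05 is a quarter of it.
- Probability that a random member of one group scores above a random member of the other, Φ(d/√2): 0.514 at d = .05 and 0.638 at d = 0.50. At .05 the groups are practically indistinguishable.

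**Step 2: pass rate when there is no true difference**

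SE = √(1/n₁ + 1/n₂), and P(estimated d ≥ c) = P(t with N−2 df ≥ c/SE).

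Example, 26/25: SE = √(1/26 + 1/25) = 0.280. For c = .05, t = 0.179 and P = 43.0%. For c = 0.50, t = 1.785 and P = 4.0%.

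| Split (N=51) | SE | d≥.05, expected direction | d≥.05, either direction | d≥0.50, expected direction |
|---|---|---|---|---|
| 26/25 | 0.280 | 43.0% | 85.9% | 4.0% |
| 31/20 | 0.287 | 43.1% | 86.2% | 4.4% |
| 36/15 | 0.307 | 43.6% | 87.1% | 5.5% |
| 41/10 | 0.353 | 44.4% | 88.8% | 8.1% |
| 46/5 | 0.471 | 45.8% | 91.6% | 14.7% |

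**Step 3: pass rate when the true d is 0.2** (noncentral t). At 26/25, 70% pass the printed rule and 15% pass d≥0.50. At 41/10 the figures are 67% and 20%.

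**Step 4: sensitivity**
- N = 50: 43.0-45.8% pass d≥.05 for splits from 50:50 to 90:10.
- N = 100: 40.2-44.1% pass d≥.05 over the same splits, against 0.7-6.8% at d≥0.50.
- Skewed scores, which the article expects (lognormal, 100,000 simulated samples, N = 51, splits 26/25, 36/15 and 41/10): 43-49% pass d≥.05, against 4-6% at d≥0.50.

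The pass rate at .05 depends little on the assumed split, sample size or distribution, because the threshold is small compared with the standard error.

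**The case against.** The strongest reply is that this is a printing slip and not a badly chosen rule. The words state the intent and match the row above. The exploratory factor analysis entry in the same column prints P>.5 for the chi-square test. That entry and this one are the only decimals in Table 2 without a leading zero, which would fit an exchange of .5 and .05. An analyst following the words would not accept d = .05. This is plausible, but the article cannot confirm it, and the published criterion needs correcting either way.

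The reply also limits the consequence. A reader might infer that construct validity would be declared for a scale unrelated to daily impact, or that the known-groups test can never fail. The article supports neither:
- Known groups is one of two construct-validity rows. The other asks for correlations of at least 0.30 with three comparators, and no rule makes the known-groups row sufficient.
- The final content is agreed with the advisory groups on all the evidence collected, and the psychometric evidence is described as preliminary.
- With no true difference, the directional rule still fails about 57% of the time at n=51. The 43% rests on a directional reading that the table does not print.

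It is also fair that 0.5 is an outside convention. The contradiction does not depend on it, since the table's own 0.30 and 0.2 yardsticks show the same thing. An article may leave the direction and the confidence interval to a fuller plan, so their absence is not counted as an error here. They belong to the repair only.

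**Conclusion.** The criterion is wrong as printed: the number contradicts its own label and the other yardsticks in the table. At n=51, for assumed splits between 26/25 and 41/10, a scale with no true separation meets d≥.05 in the expected direction in 43-44% of samples, against 4-8% at d≥0.50. Without regard to direction the printed rule is met in 86-89% of samples, rising to 92% at 46/5.

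The known-groups row is therefore nearly uninformative by itself. The damage stops there: the three correlation criteria are untouched and no sample-size calculation uses this threshold. The figures rest on the assumed splits, on applying the threshold to the point estimate, and on a pooled-SD d. The skewed-data check leaves the conclusion unchanged.

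**What to change.** Correct the Table 2 entry to d≥0.50 and state that the group reporting impact on daily activities is expected to score higher. The stage 3 analyses are already complete, so the correction should document, from records that predate the analysis, that 0.50 was the intended value. A threshold chosen after seeing the data would not carry the same weight. The stage 3 paper should judge the known-groups result against that value and report d with its 95% CI.

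The cost is one table entry or an erratum, and a stricter criterion. Applied to the point estimate at n=51, d≥0.50 is met about 50% of the time when the true d is 0.5, and 80-86% of the time when it is 0.8 (splits 41/10 to 26/25). The confidence interval is therefore needed to interpret a near miss as well as a pass.

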### Stage 4: Preliminary Measures of Change

#### Overview

In order to provide initial insights into meaningful change scores on the new symptom burden scale, a mixed methods approach will be used. First, the draft PROM will be readministered to all participants from stage 3, alongside a global measure of perceived change in health status, after 2 months (informed by expert clinical opinion). This will allow estimates of stability (test-retest reliability and measurement error) in those without change, and estimates of change (responsiveness, minimal important change [MIC], otherwise known as meaningful score difference [58]) in those with change. Second, as iMCD is a rare disease, it is possible that insufficient participants are recruited at follow-up and/or insufficient change is observed to reliably estimate the MIC. Accordingly, in addition to quantitative estimates, semistructured qualitative debriefing interviews will be carried out with patients who have completed the survey at both time points to understand what constitutes a meaningful improvement from the patients’ perspective [19,20]. By triangulating this information with expert advisory input, the aim is to provide preliminary evidence on meaningful change using a natural history (ie, noninterventional) approach.

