#### Data Collection

All stage 3 participants will receive an invitation with a link to the stage 4 online survey by email 2 months after they initially completed the survey. The stage 4 survey is a reduced form of the stage 3 survey, omitting most of the background questions (only questions on treatment remain) and the questions on the importance of symptoms. In addition, in order to measure and benchmark clinical change (or lack thereof) in participants’ perceived health, a self-report global impression of change will be used as the primary anchor [59]. The health transition item from the Short Form 36 Health Survey (ie, compared to when you last completed this questionnaire, would you say your overall health has improved a lot, improved somewhat, stayed the same, worsened somewhat, or worsened a lot) will be adapted to estimate changes in health status [60]. Global anchors capture the multidimensional experience of health and are widely used and understood. However, as a secondary construct-specific anchor, existing estimates of MIC for PHQ-15 and/or preestablished clinical cutoffs for the measure will be used [55,61].

Using a semistructured topic guide (Multimedia Appendix 3), the supplementary cognitive interviews are intended to identify meaningful changes from the patients’ perspective. Specifically, after consent procedures, participants will complete the shortened (finalized) version of the novel PROM to refamiliarize themselves with the instrument. They will then be shown their symptom profile (and overall burden score) from the stage 4 survey on screen. Participants will then be asked questions to identify what the minimum improvement in their symptom profile would be for them to consider meaningful. Finally, participants’ understanding of the global impression of change anchor (and what influenced their response) will be explored to help understand the quantitative results.

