#### Analysis

As this study uses a natural history framework for exploring change (ie, it is noninterventional), all change statistics should be considered informative but preliminary only. Reliability and measurement error statistics can be calculated in the subsample of participants whose health status “stayed the same” between stage 3 and stage 4. Specifically, the intraclass correlation coefficient will be used to assess test-retest reliability, while the standard error of measurement and minimum detectable change at the 95% confidence level will be used to estimate measurement error in “stable” participants.

Preliminary analyses of responsiveness (ie, in the absence of an intervention) will be estimated using the standardized response mean (for improved, stable, and worsened participants) and the receiver operating characteristic area under the curve for the improved subgroup.

To estimate improvement-based MIC, the mean and median change in symptom burden (between stage 3 and stage 4) among participants who reported a minimal improvement in health (ie, “improved somewhat”) will form the primary anchor-based MIC. A secondary anchor approach will compare change in symptom burden with change in PHQ-15 scores, with an “improved” group defined by (1) a PHQ-15 score greater than or equal to the estimated MIC for the PHQ-15 of 3 points [61] and/or (2) categorical improvement in PHQ-15 clinical cutoff groups (eg, from “moderate” to “mild” symptoms) [55]. These anchor methods will be supplemented with distribution-based analyses using standard approaches (ie, 0.5 × SD and standard error of measurement) [59]. Change in worsened groups will be calculated and reported for comparative purposes but is not the primary focus of interest. Finally, responder difference will be estimated using (1) the binary method, whereby the proportion of people in improved vs not improved subgroups experiencing improvement above the MIC is estimated; and (2) the mean method, whereby the difference in mean burden change for the improved vs not improved subgroups is calculated [62].

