Smaller samples are inevitable in rare disease research, and this limits what can be done in terms of psychometric analysis. The multinational approach of the ISBUS project helps to address this, but implicit in this approach is the assumption that the survey operates equivalently across different primarily English-speaking countries (due to the expected small sample sizes from different countries, it may be impractical to test this assumption formally). While samples could be expanded by recruiting patients with sufficiently analogous conditions [20], this decision risks undermining the goal of the novel PROM and its unique applicability to people living with iMCD. Instead, methods will be adapted for smaller samples, with any limitations transparently noted during dissemination [30]. In addition to the smaller sample size being challenging, the fact that iMCD is an episodic condition in which symptom burden is related to the activity of the disease and the treatment that the patient is receiving means that the timing of survey administration is important. We aim to address this by enrolling as many patients as possible in the hope that patients experiencing initial flares, relapses, and remissions will all be captured.

Another limitation to consider is the reliance on self-reported diagnosis. However, methods including a robust, clinically informed screener and dual recruitment routes (ie, via the CDCN and clinically verified patients with iMCD) help to offset this. Further, the reliance on online data collection is a pragmatic and advisable choice in rare disease research [19], but may limit inclusion of those who choose not to, or are unable to, take part in online studies. Reassuringly, research suggests switching from online to paper-based administration (or vice versa) is likely to have only a minor influence on responses [52]. Finally, the estimates of change in stage 4 should be considered preliminary only, as they are derived from a natural history approach (ie, noninterventional). While our approach is strengthened by triangulation of multiple methods, estimates such as the standardized response mean (responsiveness) may form a lower bound of sensitivity to change (as no direct study intervention was administered) and should be considered conservative.

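### The only numeric criterion for the primary change anchor can be met by a rating of current health alone, so meeting it does not show that the anchor measures change

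*Protocol article*

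**What the plan says.** In the article's Stage 4 Data Collection section, "a self-report global impression of change will be used as the primary anchor". The item reads "compared to when you last completed this questionnaire, would you say your overall health has improved a lot, improved somewhat", followed by unchanged and worsened options. It is asked once, in the follow-up survey two months after stage 3, alongside the second ISBUS.

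Under Stage 4 Analysis, the mean and median ISBUS change among those who improved somewhat "will form the primary anchor-based MIC". The unchanged group gives the ICC, the standard error of measurement and the MDC95. The SRM and ROC AUC are also computed in improved, stable or worsened groups.

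In Table 2 the criterion beside the anchor-based MIC is "Correlation between anchor and change ≥0.30".

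Two further elements bear on the anchor. In the stage 4 interviews, participants' "understanding of the global impression of change anchor (and what influenced their response) will be explored". A secondary anchor uses change in PHQ-15, which is measured at both surveys.

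Strengths and Limitations says of estimates such as the SRM that they "may form a lower bound of sensitivity to change (as no direct study intervention was administered) and should be considered conservative".

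**The concern.** A transition question asks the patient to compare today with a remembered state two months back. In an episodic disease the answer may follow how the patient feels today. A criterion for the anchor should separate that case from a genuine rating of change, and a correlation with the change score does not, because the stage 4 score is part of the change score.

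The MIC, the stable group (ICC, SEM, MDC95), the SRM and the AUC all use this item to form groups. If it is mainly a current-state rating, the mean change in those who improved somewhat depends on the retest correlation rather than on what patients regard as a small worthwhile improvement. The conservative label on the SRM has the same weakness: the groups are selected on the patient's own stage 4 rating, and that selection can raise the SRM among improvers.

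**Working it through.** **Inputs from the article.** Criterion 0.30 (Table 2). Minimum 20 follow-ups (Stage 4 Participants and Recruitment); 32 completed by March 2026 (Results). The threshold is set, not derived, so there is no plan figure to reproduce.

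**Assumptions (the article gives none of these).** Y1 and Y2 are ISBUS at stages 3 and 4, higher meaning worse, with correlation r. Improvement is Y1−Y2. The anchor is scored so that higher means better. It depends on Y2 only, with tracking strength v = |corr(anchor, Y2)|.

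**1. Correlation with change, equal SDs.**
corr(anchor, Y1−Y2) = v(1−r)/√(2(1−r)) = v√((1−r)/2).
- v=1: 0.50, 0.45, 0.39, 0.32 and 0.22 at r=0.5, 0.6, 0.7, 0.8 and 0.9.
- The value is at least 0.30 when r ≤ 1 − 2(0.30/v)². For v=1 this is 1 − 0.18 = 0.82; for v=0.8, 0.72; for v=0.6, 0.50; for v=0.5, 0.28.

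**2. Unequal SDs.** With k = SD2/SD1 and v=1, the correlation is (k−r)/√(1+k²−2rk). At r=0.7:
- k=0.8: 0.1/√0.52 = 0.14
- k=1: 0.39
- k=1.2: 0.5/√0.76 = 0.57

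**3. Chance of passing with n=32.** Simulation with normal scores, Spearman correlation and a five-level anchor split 10/20/40/20/10% (assumed):

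| Tracking v | r=0.6 | r=0.7 | r=0.8 |
|---|---|---|---|
| 1.0 | 75% | 66% | 48% |
| 0.8 | 58% | 47% | 36% |
| 0.6 | 39% | 32% | 24% |

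For comparison, under a 5/20/50/20/5% split, an anchor unrelated to ISBUS passes in about 5% of studies at n=32 and 10–12% at n=20.

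**4. What the MIC would be.** Given Y2, the expected Y1 is rY2, so mean improvement in a group is (1−r) times how far its mean stage 4 score lies below average. Under the same split, the improved-somewhat group lies between the 70th and 90th percentiles, with mean 0.86 SD. At r=0.6 and v=1 the MIC is 0.4 × 0.86 = 0.34 SD (simulated 0.35). At v=0.8 it is 0.8 × 0.34 = 0.28 SD. It is fixed by r and v. At r=0.6, SRM≥0.2 in improvers is then met in about 86% (v=1) and 77% (v=0.8) of studies, although the anchor holds nothing beyond the stage 4 score.

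**5. What would tell the two apart.** Five-level anchor, r=0.7, split 5/20/50/20/5%:

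| Anchor | With Y1 | With Y2 |
|---|---|---|
| Tracks change (latent correlation 0.7) | +0.25 | −0.25 |
| Tracks current state (v=1) | −0.66 | −0.94 |

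The second anchor still correlates 0.35 with change and meets the criterion.

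Partial correlation with Y1 given Y2, on the latent scale:
- Current-state anchor: the numerator is −vr − (−v)r = 0.
- Change anchor, latent correlation 0.7, r=0.7: c = 0.7 × 0.387 = 0.271, and the partial is 0.271 × 1.7/√((1−0.073)(1−0.49)) = 0.461/0.687 = 0.67.

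**6. Why not a gate.** At n=32, requiring opposite raw signs rejected a genuine change anchor (latent correlation 0.5–0.7) in about 12–43% of simulated studies. Requiring only a positive partial sign accepted a pure current-state anchor in about 40%, because its expected value is near zero.

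**The case against.** **Other checks exist.** A reader might infer that 0.30 is the only test of the anchor. It is not: the interviews ask directly what influenced the answer, and the PHQ-15 anchor is built from two measurements. This stands, and limits the point to the only numeric criterion for the anchor. The interviews carry no decision rule, and the PHQ-15 anchor is secondary.

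**Other rows of Table 2 would protest.** A reader might infer that the plan would certify a current-state anchor. With v of 0.8 to 1, the stable-group ICC≥0.70 was met in only about 0–13% of simulated studies at r=0.6–0.7. This largely stands, with two reservations. The plan does not read a low ICC as evidence about the anchor, so the scale would be blamed. The signal also fades: at r=0.8 and v=0.7 the large-sample stable-group ICC is 0.71. MIC below MDC95 is not diagnostic, since that row fails under a genuine change anchor too.

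**Strong tracking may be unrealistic.** The item asks about overall health, and the article expects at least moderate correlations (0.30 or more) between ISBUS and EQ-5D-5L. That is a floor and does not settle v, but it is a fair reason to write that the criterion can be met, not that it is met.

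**Enrolment in flares.** A reader might infer that regression to the mean pushes the SRM upward. Strengths and Limitations hopes to capture remissions as well as flares, and remissions regress the other way. No direction follows.

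**Preliminary status and unseen documents.** All change statistics are called preliminary and the final value is triangulated. A separate analysis plan may already hold the extra correlations. The point therefore rests on a criterion and a claim that the article does state, not on an omission.

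**Conclusion.** The concern holds in limited form. Meeting 0.30 does not by itself show that the transition item measures change, because a current-state rating can meet it. With equal SDs and perfect tracking this is so up to r=0.82. With tracking of 0.8 the limit is 0.72, and with 0.6 it is 0.50; a smaller stage 4 SD lowers it further. At n=32 the chance of a false pass is roughly 24% to 75% for tracking of 0.6 to 1 and r of 0.6 to 0.8. Those ranges, the SD ratio and the category split are assumptions.

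The documents do not show that the anchor is in fact a current-state rating, or that the SRM is biased upward. They also do not support calling the SRM conservative: absence of an intervention is one reason for a smaller SRM, but selection on the patient's own stage 4 rating can work the other way. The consequence is moderate, given the triangulation and the preliminary label, and the remedy costs almost nothing.

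**What to change.** 1. In Table 2, anchor-based MIC row, keep the 0.30 criterion and add: report, with confidence intervals, the anchor's Spearman correlation with the stage 3 ISBUS score, with the stage 4 score, and its partial correlation with stage 3 given stage 4.
2. State how these are read, as graded evidence and not pass/fail. If the stage 3 and stage 4 correlations share a sign and the partial correlation is near zero, flag the transition-item MIC, and the stable-group and SRM results built on it, as possibly driven by current state. Give the PHQ-15 change anchor and the interview estimates more weight in the triangulation.
3. In Strengths and Limitations, replace the lower-bound and conservative wording with a statement that the direction of bias in the SRM is uncertain, because the groups are selected on the patient's own stage 4 rating.

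The cost is three correlations on scores the two surveys already collect, and one reworded sentence. As stage 4 was still under way at submission, the reading rule should be fixed before those results are examined. The downside is that the transition-item MIC may have to carry a caveat, and with about 32 participants the intervals will be wide.
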